**10 STATISTICAL STATEMENT**

**10.1 Statistical Hypothesis**

Study hypotheses:

i) Cure rate of resistant malaria after Cotrifazid treatment is not inferior to the one obtained after treatment with mefloquine or quinine and Fansidar.

ii) Cotrifazid is safe to use in semi-immune patients with resistant malaria. No IRAE attributable to the drug is expected in the subjects.

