**1.2 Objectives of the Trial**

The purpose of this trial is to assess the efficacy and safety (primary parameters) of Cotrifazid in semi-immune Papua New Guinean patients with resistant malaria.

More specifically i) to compare the efficacy of Cotrifazid versus Lariam (mefloquine) or standard treatment in semi-immune subjects with resistant malaria, and ii) to compare the tolerance of Cotrifazid versus Lariam or standard treatment in semi-immune subjects with resistant malaria.

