**10.2 Study Design**

This is a multicentric, open, block-randomised, comparative study.

1. **Sample Size Calculation**

The overall sample size of 330 (110 in Cotrifazid group, 110 in Lariam group and 110 in standard treatment group) is sufficient to demonstrate that Cotrifazid is not inferior to Lariam or quinine and Fansidar, assuming a rate of treatment success of 95% with Lariam or quinine and Fansidar and a clinically acceptable rate of treatment success of 86% or more in the Cotrifazid group, a 10% loss of follow-up (80% power, 95% confidence limits, one-sided test) (formula from Jones et al, 1996).

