**10.4.2 Primary Safety Parameters**

Rates of acute and subacute AEs by severity and relation to the drug will be compared between the Cotrifazid and the comparator groups. Laboratory parameters (haematological) in the two groups will be compared.

The Mantel-Haenzel Chi-square test (x2=0.05, two-tailed) will be used to assess any significant difference between the two groups in terms of number of AEs reported.

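### Section 10.1(ii) hypothesises that Cotrifazid is safe, but the only safety test named is a test of difference, with no acceptable excess, bound or safety power, and it cannot confirm that claim

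*Protocol*

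**What the plan says.** Section 1.2 of the protocol names efficacy and safety together as the primary parameters. Its second objective is comparative: "to compare the tolerance of Cotrifazid versus Lariam or standard treatment in semi-immune subjects with resistant malaria".

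Section 10.1 turns this into an absolute statement followed by an expectation: "Cotrifazid is safe to use in semi-immune patients with resistant malaria. No IRAE attributable to the drug is expected in the subjects". It names no comparator, acceptable rate or margin.

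Section 10.4.2 gives the analysis. It is comparative: "Rates of acute and subacute AEs by severity and relation to the drug will be compared between the Cotrifazid and the comparator groups". The only test named is one of difference: "The Mantel-Haenzel Chi-square test (x2=0.05, two-tailed) will be used to assess any significant difference" in the number of AEs reported.

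The sample size paragraph (10.3 in the table of contents) allots "110 in Cotrifazid group, 110 in Lariam group and 110 in standard treatment group". It rests on 95% success with the comparators, a lowest acceptable 86% with Cotrifazid, 10% loss, 80% power and a one-sided test. It contains no safety quantity.

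**The concern.** The objective, the hypothesis and the test do not line up. The objective is to compare tolerance, the hypothesis asserts safety without a comparator, and the test looks for a difference.

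A test of difference can reject equality. It cannot establish that a drug is safe, because a non-significant result is compatible with no excess and also with an excess the trial was too small to see. The protocol respects this distinction for efficacy: hypothesis (i) is one of non-inferiority, with a lowest acceptable success rate and a power calculation. Hypothesis (ii) has no counterpart to any of these.

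The expectation of no attributable IRAE does not fill the gap. An observed zero bounds the rate only loosely at this sample size, and by itself says nothing about how Cotrifazid compares with mefloquine or quinine plus Fansidar. At stake is the wording of a primary conclusion: whoever reports against 10.1(ii) has to say whether safety was confirmed, and the plan supplies nothing that could confirm it.

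**Working it through.** **Inputs from the protocol.** 110 patients per arm, 10% loss, 95% and 86% success, 80% power, one-sided 95% confidence (10.3); two-tailed 5% chi-square for AEs (10.4.2); safety population requiring at least one daily dose and one follow-up visit (section 9). I use 110 and 110 × 0.9 = 99 per arm as the range.

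**Assumptions.** The protocol gives no AE or IRAE rates, so all rates below are mine. AEs are counted as patients with at least one AE, and Cotrifazid is set against one comparator.

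**1. The plan's own figure.** With equal true success of 95% and a margin of 95 − 86 = 9 points, n per arm = 2 × 0.95 × 0.05 × (z₁ + z₂)² / 0.09².
- z₁ = 1.645, z₂ = 0.842 (80% power): 0.095 × 2.487² / 0.0081 ≈ 72.5, so 73; 73 / 0.9 gives 82.
- z₁ = 1.645, z₂ = 1.282 (type II error halved, as in equivalence formulas): 0.095 × 2.926² / 0.0081 ≈ 100.4; 100.4 / 0.9 = 111.6, close to 110.

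On either calculation 110 is about enough for efficacy, and neither contains a safety input.

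**2. What zero attributable IRAEs would show.** One-sided 95% upper bound after 0 of n: 1 − 0.05^(1/n).
- n = 110: 2.7%
- n = 99: 3.0%

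Probability of seeing none at true rate p: (1 − p)^n.

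| True rate | n = 110 | n = 99 |
|---|---|---|
| 0.1% | 90% | 91% |
| 0.5% | 58% | 61% |
| 1% | 33% | 37% |
| 2% | 11% | 14% |
| 3% | 3.5% | 4.9% |

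Zero is the likelier result only below 1 − 0.5^(1/n), which is 0.6% (n = 110) or 0.7% (n = 99).

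**3. What the AE test would miss.** Full enumeration of two independent binomials; Mantel-Haenszel chi-square with factor N − 1; critical value 3.841; a detection is a significant result in the direction of harm.

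| Comparator vs Cotrifazid AE rate | Missed, 110 per arm | Missed, 99 per arm |
|---|---|---|
| 5% vs 10% | 70% | 73% |
| 20% vs 30% | 60% | 63% |
| 10% vs 20% | 44% | 49% |
| 5% vs 15% | 27% | 32% |
| 10% vs 25% | 15% | 19% |

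**4. What estimation would deliver.** Half-width of the 95% CI for the rate difference at equal rates p: 1.96 × √(2p(1 − p)/n).
- p = 5%: 5.8 points (n = 110) to 6.1 (n = 99)
- p = 10%: 7.9 to 8.4
- p = 20%: 10.6 to 11.1

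After zero IRAEs, the upper limit of the two-sided exact 95% interval, 1 − 0.025^(1/n), is 3.3% (n = 110) or 3.7% (n = 99).

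**The case against.** A reader might infer that the protocol will declare Cotrifazid safe if no attributable IRAE occurs and the AE test is non-significant. The text does not support that. Section 10.1 gives a hypothesis and, separately, an expectation. Section 10.4.2 says only that the test "will be used to assess any significant difference between the two groups in terms of number of AEs reported". Nothing ties either result to a safety verdict. Likewise, one attributable IRAE would contradict an expectation; it is not a stated failure criterion.

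A reader might also infer that 110 per arm would usually miss relevant harm. That depends on the size of the excess, which the protocol does not define. It holds for 5% against 10% or 20% against 30%. It does not hold for 10% against 20%, which is detected slightly more often than not, or for 10% against 25%. At a true IRAE rate of 1%, at least one event is seen with probability 67% (63%). The 80% power in 10.3 belongs to efficacy, so it is not a standard that the safety test breaches.

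The safety plan is also wider than one test. The synopsis lists AE rate, AE type, additional drugs needed for tolerance problems, and laboratory results; 5.2.1 puts close observation first; and 5.2.3 requires every IRAE, related or not, on the AE page, so IRAEs enter the comparison between arms. Sizing on efficacy alone is normal, and intervals are often left to an analysis plan.

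All of this stands, and it limits the point. It does not answer it: the hypothesis is worded in the protocol, and an analysis plan that added intervals would still inherit a claim that the named test cannot confirm.

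**Conclusion.** The point holds as a mismatch between a positive claim of safety and a test of difference. Neither of the two results in view, no attributable IRAE or no significant AE difference, could confirm 10.1(ii).

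The bound on the attributable IRAE rate after zero events needs only the number of patients, 99 to 110. The miss rates for AEs rest on assumed rates, per-patient counting and one comparator at a time, and they run from 70% (73%) down to 15% (19%) as the excess grows. They show that a non-significant test would be weak evidence against a moderate excess. They do not show that the trial is blind to harm.

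The change should be made, because safety is a primary purpose. Trial conduct and the efficacy sample size are not affected.

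**What to change.** - **10.1(ii):** replace the statement of safety with comparative estimation in line with objective (ii). For example: to estimate the difference in the proportion of patients with an AE between Cotrifazid and each comparator, and the rate of patients with an IRAE in each arm.
- **10.4.2:** base the safety conclusion on that difference, against Lariam and against standard treatment separately, with its 95% CI, and on the IRAE rate (all and attributable) per arm with exact 95% limits. The chi-square test may stay as a supplement. State that a non-significant test or zero events will not be taken as proof of safety.
- **10.3 (optional):** add one sentence on what the sample size can show for safety, namely that zero events in 110 (99) patients excludes only a rate above 2.7% (3.0%), one-sided 95%.

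The cost is wording in these sections and a few more intervals, with no extra patients, visits or data. The downside is a weaker safety claim, with intervals that will be wide.

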**10.2 Study Design**

This is a multicentric, open, block-randomised, comparative study.

1. **Sample Size Calculation**

The overall sample size of 330 (110 in Cotrifazid group, 110 in Lariam group and 110 in standard treatment group) is sufficient to demonstrate that Cotrifazid is not inferior to Lariam or quinine and Fansidar, assuming a rate of treatment success of 95% with Lariam or quinine and Fansidar and a clinically acceptable rate of treatment success of 86% or more in the Cotrifazid group, a 10% loss of follow-up (80% power, 95% confidence limits, one-sided test) (formula from Jones et al, 1996).

**10.4 Strategy for Statistical Analysis**

**10.4.1 Efficacy Parameters**

**10.4.1.1 Primary Efficacy Parameters**

Efficacy will be estimated by comparing the rate of treatment failure, and proportions of complications between the Cotrifazid and comparator groups, using the Mantel-Haenzel Chi-square test (x2=0.05, one-tailed). The time to fever clearance and the time to parasite clearance will also be compared between the Cotrifazid and comparator groups. Survival curves showing the clearance time will be plotted for the two groups, and compared using the logrank test.

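### The cure-rate hypothesis is non-inferiority, but the test named for treatment failure compares equal rates without the margin and so cannot answer it

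*Protocol*

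**What the plan says.** Protocol 10.1 gives the efficacy hypothesis: "Cure rate of resistant malaria after Cotrifazid treatment is not inferior to the one obtained after treatment with mefloquine or quinine and Fansidar".

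The sample size paragraph (10.3 in the contents, printed under 10.2) follows the same aim. It sets "The overall sample size of 330 (110 in Cotrifazid group, 110 in Lariam group and 110 in standard treatment group"). For the comparators it works from 95% success, and for Cotrifazid it asks for "a clinically acceptable rate of treatment success of 86% or more in the Cotrifazid group". It also allows for "a 10% loss of follow-up". The error rates are given as "80% power, 95% confidence limits, one-sided test".

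Section 10.4.1.1 fixes the analysis. The outcomes compared between Cotrifazid and the comparators are treatment failure and complications, and the method is named with the words "using the Mantel-Haenzel Chi-square test (x2=0.05, one-tailed"). The section mentions neither the 86% nor a margin, compares no confidence limit with one, and does not say in which direction the single tail lies or which result would support the hypothesis. Section 10.4.2 uses the same test, two-tailed, to look for a difference in adverse events.

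**The concern.** A non-inferiority claim needs evidence that the new drug is not worse by more than a stated amount. A chi-square test of equal failure rates has a different null hypothesis, and neither of its outcomes provides that evidence.

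- A non-significant result shows only that a difference was not detected. Used as the criterion, it makes the claim easier as the data get sparser. That matters here because section 9 removes patients without full dosing from the efficacy population and section 6.2 rules out replacement.
- A significant result in favour of Cotrifazid shows superiority, which the trial neither hypothesises nor is sized for.

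Either way, the planned power belongs to an analysis that 10.4.1.1 does not specify. An analysis plan that followed the protocol faithfully would inherit the mismatch. One that departed from it would contradict the protocol.

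**Working it through.** **Inputs.** From the sample size paragraph: comparator success 95%, lowest acceptable Cotrifazid success 86%, 110 per arm, 10% loss (110 × 0.9 = 99 evaluable), one-sided 5%, 80% power. The margin is derived: 95 − 86 = 9 points.

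**1. Is 110 a non-inferiority number?** For equal true rates of 95%, n = 2 × 0.95 × 0.05 × (z₁₋α + z_power)² / 0.09².
- z = 1.645 and 0.842: n = 72.5, so 73, and 82 after 10% loss.
- z = 1.645 and 1.282 (the β/2 form used for equivalence, numerically 90% power): n = 100.4. This becomes 111.6 on dividing by 0.9, or 110.5 on multiplying by 1.1, which reproduces 110.
- A one-sided test of difference, 95% v 86%: 131, or 146 after loss. This does not reproduce 110.

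So 110 fits a margin of 9 points and does not fit the test in 10.4.1.1. The literal inputs need fewer patients, so the size is sufficient.

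**2. Non-significance read as not inferior.** Take true success 86% v 95%. With x and y failures on Cotrifazid and comparator and n per arm, put t = x + y and N = 2n. Then Z = (x − t/2)/√V, with V = n² t(N − t)/[N²(N − 1)]. Sum the two binomial probabilities over all outcomes with Z < 1.645 (single stratum).

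| Evaluable per arm | No continuity correction | With correction |
|---|---|---|
| 99 | 28.0% | 37.4% |
| 110 | 24.0% | 33.9% |

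Check by normal approximation at n = 99: standard error under the null √(2 × 0.905 × 0.095/99) = 0.0417; under the alternative √[(0.95 × 0.05 + 0.86 × 0.14)/99] = 0.0412. Then (0.09 − 1.645 × 0.0417)/0.0412 = 0.52, so power is about 70% and non-significance about 30%, close to the exact 28%.

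Sparser data raise the rate: 36% at 80 per arm and 47% at 60.

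These are rates per comparison. With the shared Cotrifazid arm and 99 per arm, non-significance against both comparators occurs in 14.3% of trials and against at least one in 41.7%.

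**3. Significance in favour of Cotrifazid required.** With both true rates 95% and n = 99, the test succeeds in 5.7% of trials. At a true 86% it succeeds in about 0%.

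**4. Example.** Failures 11/99 on Cotrifazid and 5/99 on comparator.
- t/2 = 8; V = 99² × 16 × 182/(198² × 197) = 3.70; Z = 3/1.92 = 1.56, below 1.645, so not significant.
- Excess failures: 11.1% − 5.1% = 6.1 points. Standard error √(0.111 × 0.889/99 + 0.051 × 0.949/99) = 0.0385.
- One-sided 95% upper limit: 6.1 + 1.645 × 3.85 = 12.4 points (Wald), or 13.0 points by the score method. Both exceed 9.

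**5. A margin-based limit at the planned size.** Claim non-inferiority if the one-sided 95% limit excludes a 9-point deficit. Exact enumeration at n = 99:
- Wald limit: claim made in 5.9% of trials at 86% v 95%, and in 89% at equal 95% rates.
- Score limit (same sum, with the variance taken at the rates fitted under a 9-point difference): 4.7% and 84%.

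**The case against.** Several points against this deserve weight.

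- A reader might infer that the trial will wrongly pass Cotrifazid 28% of the time. The document does not support that as a fact. It gives no decision rule and no direction, and under the superiority reading a drug at 86% passes almost never. The 28% is conditional, and it is a rate per comparison; the trial-level rate depends on whether one comparator or both must be satisfied, which 10.1 leaves open with its *or*.
- A reader might call 86% an unacceptable rate. The protocol calls it acceptable. It is the edge of the acceptable range, and it serves as the null boundary only in the non-inferiority test.
- The protocol never uses the word margin. The 9 points rest on the assumed 95%. If comparator success were, for illustration, 88%, a fixed 9-point margin would tolerate 79%, below the stated 86%.
- A reader might extend the criticism to the logrank tests of clearance times and the t test of haemoglobin. Section 10.1 states non-inferiority for cure rate only, so difference tests on those outcomes contradict no stated hypothesis.
- The sample size paragraph speaks of one-sided 95% confidence limits, which suggests that a confidence-limit approach was in mind at the design stage.

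All of this limits how the size may be stated. None of it rescues 10.4.1.1. The section names a specific test, tail and level, and nothing in it signals a null shifted by a margin.

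**Conclusion.** The mismatch is real and stands in the current text: a non-inferiority hypothesis and sample size are paired with a test of equal failure rates that ignores the margin. That conclusion depends on no percentage.

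Its size depends on the reading. If non-significance counts as not inferior, the false-claim rate at the boundary of the acceptable range is about 28% per comparison, with a range of 24% to 37%, against the 5% implied by one-sided 95% limits. This assumes 99 evaluable per arm, no continuity correction and a single stratum; the range covers 110 per arm and the corrected test. If significance in favour of Cotrifazid is required, the error is not inflated, but the claim succeeds only about 6% of the time when the drugs are equally good at 95%.

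The number of patients is not at fault: 110 per arm is enough for the analysis that the hypothesis calls for. The text should be corrected before the analysis.

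**What to change.** In 10.4.1.1, for the treatment failure (cure) rate only:

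1. Replace the chi-square as the basis for the conclusion with a one-sided 95% confidence limit, by a score method such as Farrington-Manning or Miettinen-Nurminen, for the difference in success, Cotrifazid minus each comparator.
2. Claim non-inferiority to a given comparator only if the lower limit lies above −9 percentage points.
3. State the margin explicitly in the sample size paragraph as well. The 9 points are implied by 95% and 86%, and the sponsor must confirm them, including what applies if comparator success is well below 95%.
4. State that a non-significant chi-square on failure rate is not evidence of non-inferiority.

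The cost is wording in 10.4.1.1 and one sentence on the margin in the sample size paragraph. No extra patients, visits or data are needed: at 99 evaluable per arm and equal 95% rates, power stays above the planned 80% with either the Wald or the score limit.

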**2 GENERAL DESIGN**

**2.1 Overall Design**

This is an open, block-randomised, comparative, multicentric study.

All subjects presenting at the outpatient clinic or admitted in the ward of the Maprik Hospital and Yagaum Health Center who are diagnosed with malaria (history of fever and no other major symptom, OptiMAL test positive) and have been already treated for malaria in the last 28 days can be included if they give their informed consent and if the clinician in charge would have given the standard treatment for resistant malaria in the absence of the study. A patient should not be included if the clinician prefers to use quinine for whatever reason, if the patient has one of the symptoms or signs of complicated or severe malaria (i.e. history of recent convulsion, any neurological sign or impairment of consciousness, temperature >40 C0, heavy vomiting, haemoglobinuria, respiratory distress, bleeding, circulatory collapse, shock, jaundice, haemoglobin < 5 g/dl), has contra-indications for mefloquine (history of psychiatric disorder, epilepsy), is less than 6 months of age, or is pregnant. The patients will be randomised on the spot to have either Cotrifazid, Lariam or standard treatment (at present quinine + Fansidar). The treatment dosage and schedule for Cotrifazid will be the following : subjects > 40 kg : 2 x 2 tablets, subjects < 40 kg and > 20kg : 2 x 1 tablet, subjects < 20 kg : 2 x ½ tablet, ever 12 hours for 7 days. The treatment dosage and schedule for Lariam will be the following : subjects > 60 kg : 6 tabs (3 at hour 0, 2 at hour 8, 1 at hour 24), subjects > 40 kg and < 60 kg : 5 tabs (2, 2, 1), subjects < 40 kg and > 30 kg : 3 ½ tabs (1 ½ , 1, 1), subjects < 30 and > 20 kg : 3 tabs (1, 1, 1), subjects < 20 kg and > 10 kg : 1 ½ tabs ( ½ , ½, ½ ), subjects < 10 kg : ¾ tablet ( ¼ , ¼, ¼ ). Follow-up assessments will be done at hours 24, 48 and 72 (clinical, parasitological and pharmacological), and days 7 (clinical, parasitological, biochemical, and pharmacological) and 14 (clinical, parasitological, haematological, and pharmacological), or more intensively in case of persisting symptoms or pathological signs. Treatment will be changed to the standard treatment (at present quinine + Fansidar) if necessary (problems of tolerance, aggravation of clinical status, increase in parasitaemia etc).

All blood samples will be taken by venepuncture (2 ml).

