**3.2 Inclusion Criteria**

Willingness of the adults, parents or legal guardian for children, to give informed consent is the primary criteria for inclusion.

Other inclusion criteria will be : persons presenting at the outpatient clinic or admitted in the ward, aged > 6 months, with fever or history of fever in the last three days, and no other major symptom or sign, with a clinical diagnosis of malaria, an OptiMAL test positive (for whatever species), and with a documented (in the health book) episode of malaria treated with standard drugs in the last 28 days.

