**5.3 Assessment of Efficacy**

**5.3.1 Primary Efficacy Parameters**

The primary parameters of efficacy i) fever clearance time, ii) parasite clearance time, iii) failure rate, iv) occurrence of complications, information collected from day 1,2,3, 7 and 14.

Thick and thin blood films will be Giemsa stained and species-specific density will be counted per/200 white blood cells (WBC). Slides will be declared negative if no parasites are seen in 100 thick film fields. Parasite density per microliter blood will be calculated by multiplying the parasitemia/200 WBC by a WBC count of 10000/L in children aged < 5 years and of 8000/L in persons aged > 5 years.

1. **Secondary Efficacy Parameters**

The secondary parameters of efficacy are i) symptom clearance time, information collected at day 1,2,3, 7 and 14, and ii) haemoglobin concentration from samples collected at day 14.

1. **Assessment of Pharmacology**

Pharmacokinetics will be assessed in a small subsample of patients (5). Blood will be drawn (2 ml by venepuncture) at hour 2, 8, 16, 24, 36, 72.

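### Parasite clearance time, a primary parameter, is compared by a plain logrank test that makes no use of baseline parasite density; the test is valid but loses power if density predicts clearance

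*Protocol*

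**What the plan says.** Protocol section 5.3.1 sets the status of the endpoint: "The primary parameters of efficacy i) fever clearance time, ii) parasite clearance time, iii) failure rate, iv) occurrence of complications". For the blood films, it says that "species-specific density will be counted per/200 white blood cells (WBC") and adds: "Parasite density per microliter blood will be calculated by multiplying the parasitemia/200 WBC" by an assumed white cell count. It describes the efficacy data as "information collected from day 1,2,3, 7 and 14"; day 0 is not in that list.

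Section 10.4.1.1 fixes the analysis: "The time to fever clearance and the time to parasite clearance will also be compared between the Cotrifazid and comparator groups". The method follows: "Survival curves showing the clearance time will be plotted for the two groups, and compared using the logrank test". It names no stratum, covariate or model. A one-tailed level is attached to the Mantel-Haenszel test in that section, but no sidedness is given for the logrank.

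Entry under section 3.2 requires "an OptiMAL test positive (for whatever species"), a qualitative result with no density range, in patients from 6 months of age upwards. Section 5.1.2 randomises in blocks of 12 and mentions no density stratum. Section 2.1 comes closest to implying a pre-treatment count: "Treatment will be changed to the standard treatment (at present quinine + Fansidar) if necessary (problems of tolerance, aggravation of clinical status, increase in parasitaemia etc").

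**The concern.** Clearance time is the time until parasites can no longer be seen, and starting density is the baseline value of that same quantity. At a given rate of killing, a patient who starts higher takes longer to reach a negative slide. With no density limit at entry, any species accepted and a wide age range, starting densities may differ widely between patients.

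Two things follow if density predicts clearance time. Its variation enters the drug comparison as noise, so a true difference in clearance is harder to see. And in the single trial that is run, a chance difference in density between arms moves the clearance comparison one way or the other, with nothing in the stated analysis to correct for it.

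**Working it through.** **The plan's own figure.** The only sample size in the protocol (section 10.3) is 110 per arm for the cure rate: 95% success, 86% acceptable, so a difference of 0.09; one-sided; 80% power; 10% loss. The usual formula is n = 2p(1−p)(z_α + z_β)²/d².
- One-sided 5%, 80% power: 0.095 × (1.645 + 0.842)²/0.0081 = 72.5, so 73, or 82 after dividing by 0.9.
- One-sided 2.5%, 80% power: 93, or 104 after loss.
- One-sided 5% with the type II error split (z = 1.282): 0.095 × (1.645 + 1.282)²/0.0081 = 100.4. This gives 110.5 on multiplying by 1.1, or 113 from 101/0.9.

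The last variant comes closest to 110. None of these involves density or clearance time, and the protocol states no power for clearance time.

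**Inputs for the clearance comparison.**
- From the protocol: 110 per arm less 10% = 99; films at days 1, 2, 3, 7 and 14.
- Assumed: pairwise comparison of Cotrifazid with one comparator; one-sided 5%; correlation ρ between log density and log clearance time of 0.3, 0.5 or 0.7; log-normal clearance time with median 1.8 days and log SD 0.45; a drug effect of 0.39 SD, which puts the plain logrank near 80% power.

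**Power by simulation** (3,000 trials per setting), plain logrank against logrank stratified by density quartile. The last column is a separate simulation on the same visit days and arm size.

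| ρ | Plain | Stratified | Gain | Separate run |
|---|---|---|---|---|
| 0.3 | 78.8% | 80.4% | 1.6 | about 81 to 83% |
| 0.5 | 79.8% | 86.7% | 6.9 | about 79 to 86% |
| 0.7 | 80.0% | 92.9% | 12.9 | about 79 to 94% |

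With no drug effect, error was 4.6 to 5.1% (plain) and 4.7 to 5.2% (stratified).

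**Closed-form ceiling.** If adjustment removed all variance explained by density, power would be Φ[(0.842 + 1.645)/√(1−ρ²) − 1.645]:
- ρ = 0.3: Φ(2.487/0.954 − 1.645) = 83.2%
- ρ = 0.5: Φ(2.487/0.866 − 1.645) = 89.0%
- ρ = 0.7: Φ(2.487/0.714 − 1.645) = 96.7%

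The simulated gains are smaller, as expected with density grouped in quartiles and clearance read on a coarse grid.

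**Sensitivity to the model.** A different simulation (two-sided 5%, 1,500 runs per cell, density tertiles, clearance generated from density and an individual kill rate, a weaker drug effect) gave, at ρ of about 0.34, 0.62 and 0.76:
- plain logrank: 33%, 48%, 55%
- stratified logrank: 36%, 60%, 74%
- Cox model with linear log density: 29%, 52%, 71%

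The pattern is the same: little to gain at the weakest correlation, clear gains above it. The Cox model did worse than the plain logrank at the weakest correlation and trailed the stratified test throughout.

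**Imbalance.** The standard error of a difference in mean density, in SD units, is √(2/99) = 0.142. The chance of an imbalance above 0.2 SD in either direction is 2[1 − Φ(0.2/0.142)] = 15.9% per comparison. Given an imbalance of 0.2 SD, the one-sided error of the unadjusted test in the direction of the imbalance is P[Z > (1.645 − ρ × 0.2/0.142)/√(1−ρ²)]:
- ρ = 0.3: P(Z > 1.223/0.954) = 10.0%
- ρ = 0.5: P(Z > 0.941/0.866) = 13.9%
- ρ = 0.7: P(Z > 0.660/0.714) = 17.8%

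In the opposite direction at ρ = 0.5 it is P(Z > 2.349/0.866) = 0.3%. These are closed-form values on a continuous time scale, not on the visit grid. The two-sided simulation, which did use the grid, agrees in pattern: in null trials with an imbalance above 1.5 SE, the plain logrank rejected in 9%, 17% and 21%; with an imbalance below 0.5 SE, in 4.9%, 1.3% and 0.2%.

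**The case against.** The strongest reply is that nothing here is wrong. Patients are randomised, so the logrank needs no covariate, and its overall error is near 5% in every simulation. Trials with an imbalance are already averaged into that 5%. This stands. A reader might infer that the plain test mistakes density for a drug effect; that holds only conditionally, in a trial where an imbalance has occurred.

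Second, strata and covariates are often left to an analysis plan, and one may exist. That is fair, but section 10.4.1.1 does name the test for a primary parameter, and a stratified test would differ from what it states.

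Third, the size is assumed. The protocol gives no correlation, clearance distribution or effect, and nothing in it places the correlation at 0.5 or above. This also stands; at 0.3 the gain is negligible.

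Fourth, a reader might infer that lost sensitivity helps Cotrifazid to its non-inferiority claim. The protocol does not support that: the hypothesis in section 10.1 and the sample size in section 10.3 concern cure rate, and clearance time carries no margin.

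Fifth, one might say that the baseline count is already in hand. It is plausible, and implied by the rule on rising parasitaemia, but that could also mean a rise between follow-up films. No hour 0 film is scheduled in words.

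**Conclusion.** The point holds as one of efficiency and interpretation. For a primary parameter, the stated test leaves unused the baseline value of the quantity being cleared. The cost in power is about 1 to 3 points at a correlation of 0.3, 7 at 0.5 and 13 to 15 at 0.7, under the stated assumptions and a one-sided 5% level that the protocol does not give for the logrank. The other simulation model gave about 2, 11 and 20 points at its own correlations. Conditional on a 0.2 SD density imbalance at correlation 0.5, one-sided error is about 14% in the direction of the imbalance.

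The documents do not support calling the logrank invalid, extending the gain to the failure proportion, or doubting the cure-rate comparison on this ground. The change is worth making because it is cheap and because, in an open-label trial, fixing the adjustment in advance prevents its being chosen after the data are seen. Confidence in the size is moderate at best, since the correlation is unknown.

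**What to change.** In section 10.4.1.1, make the main comparison of parasite clearance time a logrank test stratified by hour 0 parasite density category, for example quartiles taken over all arms combined, and keep the plain logrank and the unadjusted curves as supportive. State the sidedness of the test.

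In section 5.3.1, state that the hour 0 film is counted and recorded as the baseline value. Say how a missing hour 0 count is handled (for example, as its own stratum), and how a patient with a positive OptiMAL test but a negative hour 0 film is treated, since that patient has nothing to clear. A Cox model with linear log density should not be offered as interchangeable with the stratified test.

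The cost is a sentence in 10.4.1.1, a short addition to 5.3.1 and slightly more analysis. If hour 0 films were not already intended, there is also one extra film per patient. Sample size and randomisation stay as they are.
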